## Abstract

**Background:**

Musculoskeletal disorders (MSDs) are the leading work-related health issue in Europe. While passive back-support exoskeletons have shown promise in reducing physical strain in laboratory settings, their medium-term effects under real-world working conditions remain largely unexplored. This study will assess the applicability and the medium-term effects of passive back-support exoskeletons on MSDs in the logistics and healthcare sectors.

**Methods:**

ELSA LogiCare is a multicenter, parallel-designed, randomized controlled trial. Participants will be randomly assigned in a 2:1 ratio to either an intervention group or a control group. The intervention group will be randomly assigned (1:1) to use one of two passive back-support exoskeleton models for 3 months, while the control group works unassisted as usual. We aim to recruit a total sample size of 120 participants, resulting in approximately 80 participants in the intervention group and 40 participants in the control group. Primary outcomes focus on feasibility and use of the exoskeleton, including daily wearing time. Effectiveness-related outcomes include musculoskeletal complaints after 3 months, assessed using the Cornell Musculoskeletal Discomfort Questionnaire. Secondary outcomes include physical and mental workload (NASA-Raw Task Load Index), job satisfaction (Copenhagen Psychosocial Questionnaire), cognitive performance (Wiener Testsystem), fatigue (Fatigue Scale), acceptance of exoskeletons (Technology Commitment), user satisfaction (Quest 2.0), user experience and implementation barriers (short interviews), absences due to illness, blood pressure, physical activity (Fitbit/Garmin) and dropouts. Outcomes will be assessed at baseline, every 4 weeks during, and immediately after the intervention. The study is open-label, with blinding applied to outcome assessors and data analysts only. Primary analyses will follow the intention-to-treat principle and will be conducted using mixed-effects models with repeated measures to estimate feasibility- and effectiveness-related outcomes over time.

**Discussion:**

When effectively integrated into workplace environments, passive back-support exoskeletons have the potential to significantly alleviate physical strain and enhance efforts to reduce the risks associated with MSDs. Our process evaluation can also help to understand how passive back-support exoskeletons can be successfully integrated into the logistics and care sectors.

**Trial registration:**

German Clinical Trials Register (DRKS) under the DRKS-ID: DRKS00036072.

## Administrative Information

Note: the numbers in curly brackets in this protocol refer to SPIRIT checklist item numbers. The order of the items has been modified to group similar items (see http://www.equator-network.org/reporting-guidelines/spirit-2013-statement-defining-standard-protocol-items-for-clinical-trials/).

## Introduction

### Background and rationale {6a}

Musculoskeletal disorders (MSDs) are the most prevalent work-related health issue in Europe [1]. Repetitive movements, unfavorable postures, and frequent or heavy lifting can overload the musculoskeletal system, increasing the risk of developing MSDs [2]. These disorders contribute to high absenteeism rates and result in longer periods of absence compared to other health conditions [1]. The financial costs associated with MSDs in Europe are estimated at approximately 240 billion euros, representing approximately 2% of the EU-15 gross domestic product [3]. Furthermore, MSDs significantly impair the quality of life of affected individuals [4, 5]. In response, the prevention of MSDs has become a priority in European and national occupational safety and health strategies [1].

Given the significant health and economic burden of MSDs, there is a growing demand for effective, scalable workplace interventions. Among emerging ergonomic solutions, passive back-support exoskeletons have gained attention for their potential to mitigate physical strain during manual tasks, especially for lifting tasks [6]. Unlike active exoskeletons, which are heavier and require external power sources, passive exoskeletons are lighter and rely on restoring forces from elastomers or springs for support [7]. Preliminary studies suggest that back-support exoskeletons can be effectively employed in various sectors, including logistics, industry, the military, and healthcare [8–12].

Existing evidence indicates that passive back-support exoskeletons can significantly reduce mechanical load and physical strain, as measured by muscular activity (reduced muscle activity trunk extension SMD: 0.58, *p* = 0.0001; [13]) and metabolic equivalents [12, 14–23]. Subjective parameters, such as self-efficacy, perceived usability, and perceived effort (reduced perceived musculoskeletal strain in back SMD: 0.73, *p* < 0.0001; [13]), also demonstrate positive changes [24–27]. However, the vast majority of studies have been conducted in controlled laboratory settings, using small, homogeneous samples and focusing on immediate physiological effects. There is a critical lack of real-world evidence on medium- and long-term health outcomes, user compliance, and the feasibility and real-world applicability of passive back-support exoskeletons—especially in high-risk sectors such as logistics and healthcare [28, 29]. While laboratory studies suggest beneficial biomechanical effects, little is known about sustained use, user acceptance, and barriers and facilitators to implementation under routine working conditions. A recent meta-analysis highlights the need for methodologically rigorous, prospective longitudinal studies to investigate the health effects of passive back-support exoskeletons [13]. Our study addresses this research gap by employing a prospective, randomized, controlled, and multicentered design, complemented by a pragmatic mixed-methods process evaluation focusing on feasibility, use, and user experience.

### Objectives {7}

This study has two co-primary objectives. The first co-primary objective is to assess the feasibility and practical applicability of passive back-support exoskeletons in the logistics and healthcare sectors under real-world working conditions. Feasibility will be evaluated in terms of intervention adherence (frequency and duration of exoskeleton wearing) and study retention over a 3-month period. In addition, user experience, acceptability, and perceived barriers and facilitators to implementation will be explored through qualitative interviews.

The second co-primary objective is to estimate the effectiveness of passive back-support exoskeleton use on musculoskeletal complaints over a 3-month period compared to usual work without exoskeletons. Effectiveness will be assessed as the change in musculoskeletal complaints measured by the Cornell Musculoskeletal Discomfort Questionnaire (CMDQ).

Secondary objectives include identifying organizational and individual barriers to implementation, evaluating the impact of exoskeleton use on job satisfaction, and exploring potential effects on cognitive performance.

We hypothesize that regular use of passive back-support exoskeletons over 3 months reduces musculoskeletal complaints compared to usual work without exoskeletons.

### Trial design {8}

This is a prospective, multicenter, randomized controlled trial with a waitlist control design and a 1:1:1 allocation ratio to three study arms: control, passive back-support exoskeleton model 1, and passive back-support exoskeleton model 2.

The selection of a 3-month intervention period was based on both physiological and organizational considerations. From a physiological perspective, previous studies on passive back-support exoskeletons have predominantly focused on short-term laboratory-based application or training sequences, often limited to single sessions or a few days of use [12, 14–20]. It has been suggested that potential sustained effects on musculoskeletal outcomes and user adaptation may only become apparent after several weeks of regular use [30]. A 3-month intervention period therefore allows for the assessment of effects beyond immediate or short-term responses while remaining feasible within real-world occupational settings.

From an organizational perspective, the intervention duration was determined by the limited availability of exoskeleton devices and the fixed project timeline. Under these constraints, a 3-month intervention period represented the maximum feasible duration to achieve the planned sample size while ensuring efficient use of available resources. Control participants will continue working as usual during this period and will receive the exoskeleton after completion of the intervention phase; data from this subsequent wearing period will not be included in the statistical analysis.

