During the intervention period, several assessments will be conducted at 4-week intervals. These assessments will include questionnaires and brief interviews to identify entry barriers, acceptance, and potential barriers to implementing exoskeletons in daily work routines, as well as to assess musculoskeletal complaints, fatigue, job satisfaction, and cognitive performance. A detailed list of the constructs to be assessed and their corresponding measurement methods is provided in Table 2. The study visits for data collection are identical in both groups.

**Table 2 Tab2:** Outcomes and operationalization

Outcomes	Data collection, operationalization
*Outcome evaluation*	
• Musculoskeletal complaints	• Cornell Musculoskeletal Discomfort Questionnaire, German version (D-CMDQ) [31]
• Sick days • Medical costs (estimate)	• Number of total sick days • Number of musculoskeletal-related sick days • Medical costs per musculoskeletal-related sick day
• Physical and mental workload • Work-related exhaustion • Job satisfaction	• NASA-Raw Task Load Index, German version (NASA-RTLX) [32] • Fatigue Scale (FS) [33] • Copenhagen Psychosocial Questionnaire, German version (COPSOQ) [34] • Resting heart rate (blood pressure monitor, Boso medicus) • Resting blood pressure (blood pressure monitor, Boso medicus)
• Attention and memory performance due to low physical exhaustion (subgroup, nursing)	• Vienna Test System (WTS) [35]
*Process evaluation*	
• Applicability of the exoskeletons in real-world work settings	• Wearing time of the exoskeleton in relation to the total time of daily physical activity
• Utilization of the exoskeletons • Acceptance among participants and employers • User satisfaction • User experience and implementation barriers	• Frequency and duration of wearing per week • Technology readiness short scale (TB) [36] • Quebec User Evaluation of Satisfaction with Assistive Technology 2.0 (QUEST 2.0) [37] • Brief interview

After the intervention, the control group will also be allowed to use the exoskeleton for 3 months (waiting-control design). However, this usage period will not be included in the statistical analysis.

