### Strategies to improve adherence to interventions {11c}

To support compliance and adherence, research staff will be available on request throughout the intervention period to assist participants, answer questions, and verify correct exoskeleton use. Upon enrollment, participants receive standardized information and training on the purpose of the study, correct use of the exoskeleton, and study procedures.

No additional strategies to actively promote or enforce adherence (e.g., reminders, incentives, real-time feedback on wearing time, or communication of usage data to workplaces or supervisors) are implemented. This decision was made deliberately to avoid influencing natural usage behavior and to preserve ecological validity by capturing realistic patterns of exoskeleton use under routine working conditions.

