### Participant timeline {13}

Trained research staff members will provide detailed explanations about the study objectives, processes, harms, and participants’ rights. They will respond to any questions from participants or representatives and ensure a complete understanding of the information provided. Once participants have successfully enrolled in the study, they will be randomly assigned to either the control or intervention group, followed by a baseline assessment.

The study visits for data collection are identical in both groups. During the intervention period, four assessments will be conducted: a baseline assessment with medical history collection, instructions, and training on the correct use of the exoskeleton; two follow-up assessments with questionnaires and short interviews administered at 4-week intervals; and a final assessment conducted 3 months later (Fig. 1).

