### Recruitment {15}

We assume that cooperation agreements will have to be concluded with several companies and hospitals to achieve the planned number of cases. It is planned to conduct three survey waves, each lasting 6 months (3 months of intervention followed by 3 months of exchange in the waiting-control design). As a result, a recruitment period totalling 18 months is planned.

Before the cooperation agreements are finalized, site visits will be conducted at the companies and hospitals. During the first contact between employees of the participating companies and the trial staff, information will be provided regarding the purpose and procedures of the trial. At this stage, employees will receive written information as well as detailed informed consent. After an appropriate period for consideration, participants will have the opportunity to ask questions, verification of inclusion and exclusion criteria will be conducted, and written consent will be obtained. Following this, participants will be enrolled in the trial, and the scheduling of the baseline assessment will occur.

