### Adverse event reporting and harms {22}

The interventions in this trial are expected to carry low risk. Potential adverse events related to the use of the passive back-support exoskeleton may include transient discomfort, pressure, friction, or skin irritation at points of force transmission (e.g., shoulders or hips), as well as musculoskeletal soreness associated with adaptation to wearing the device. Improper adjustment of the exoskeleton to individual body proportions may increase the likelihood of such events.

To minimize these risks, a lightweight and ergonomically adjustable exoskeleton model will be used that does not restrict the user’s range of motion. Participants will receive comprehensive initial training on correct adjustment and use of the exoskeleton, with regular checks by trial staff to ensure proper fit and safe use.

Adverse events (AEs) are defined as any unfavorable or unintended signs, symptoms, or injuries occurring during the study period, regardless of whether they are considered related to the intervention. This includes events potentially related to changes in work behavior during trial participation (e.g., musculoskeletal complaints, minor injuries, or falls occurring during routine work activities). Serious adverse events (SAEs) include events that result in death, life-threatening conditions, hospitalization, persistent or significant disability, or are otherwise considered medically serious.

All AEs and SAEs, whether solicited or spontaneously reported, as well as any unintended effects occurring from enrollment until the end of the trial, will be documented. Documentation will include onset, duration, severity, management, outcome, and the investigator’s assessment of relationship to exoskeleton use. Serious adverse events will be reported to the responsible ethics committee within 24 h of the research team becoming aware of the event.

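### The exclusion of the controls' post-week-12 wearing period from analysis makes no exception for harms, so device-related adverse events in former controls would be collected but not analysed

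*Protocol article*

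**What the plan says.** Three parts of the protocol article bear on this.

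- **Exclusion.** Under Trial design {8}, controls receive the device once the intervention phase is over, and "data from this subsequent wearing period will not be included in the statistical analysis". Intervention description {11a} repeats both halves: "After the intervention, the control group will also be allowed to use the exoskeleton for 3 months (waiting-control design"), and then "However, this usage period will not be included in the statistical analysis". Neither place limits the exclusion to particular outcomes.
- **Harms.** Adverse event reporting and harms {22} states that all adverse and serious adverse events, "as well as any unintended effects occurring from enrollment until the end of the trial, will be documented". Onset and the assessed relationship to the device are recorded. The end of the trial is not defined for the individual participant.
- **Schedule.** Recruitment {15} makes the waitlist wearing half of every survey wave, "each lasting 6 months (3 months of intervention followed by 3 months of exchange in the waiting-control design"). Participant timeline {13} closes with baseline, two follow-ups "and a final assessment conducted 3 months later", and the last column of Table 3 is week 12. Table 3 lists exoskeleton training at baseline and at the week-1 call only, in line with section {11c}: "Upon enrollment, participants receive standardized information and training on the purpose of the study, correct use of the exoskeleton, and study procedures".

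The section on the choice of comparators {6b} says the comparison will allow the safety of the device to be assessed, along with its effectiveness and usability. Section {11b} treats stopping use because of discomfort as an important study outcome.

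**The concern.** Leaving the waitlist period out of the effectiveness comparison is sound, because there is no longer an unexposed control group. The same reasoning does not carry over to harms. A worker who was randomised to control and later wears the device at work can have the pressure, friction, skin irritation or soreness that section {22} names as possible effects. That is information about the device whatever the original allocation.

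Taken together, the rules require these events to be documented and then keep them out of the analysis. The trial has an aim that includes device safety, and its own introduction says that real-world evidence is lacking, yet part of its device exposure would go unreported. The events would also be recorded less reliably than those before week 12, because no enquiry about them is scheduled. In addition, initial training is one of the stated risk controls, but no training entry coincides with the date on which controls start wearing the device.

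**Working it through.** **The plan's own figure.** Section {14} asks for 80 + 40 = 120 complete datasets and allows for up to 50% dropout. 120/(1 − 0.5) = 240, 80/(1 − 0.5) = 160 and 40/(1 − 0.5) = 80. This reproduces the stated maximum of 240 (about 160 intervention, 80 control).

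**Share of device-exposed workers left out.** Let i be the intervention participants given a device and c the controls who go on to receive one. The share is c/(i + c). I take i = 160, because intervention participants are exposed from baseline even if they later drop out, and c = 80 × (1 − dropout) × uptake. The dropout values are the retention target (25%, section {12}) and the planning figure (50%, section {14}). Uptake is not given. Section {11a} says only that controls are allowed to use the device, so 75% is shown as an assumption beside 100%.

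| Control dropout | c at full uptake | Share at full uptake | Share at 75% uptake |
|---|---|---|---|
| 0% | 80 | 80/240 = 33.3% | 60/220 = 27.3% |
| 25% | 60 | 60/220 = 27.3% | 45/205 = 22.0% |
| 50% | 40 | 40/200 = 20.0% | 30/190 = 15.8% |

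At the completer target the ceiling is the same: 40/(80 + 40) = 33.3%.

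**What the omission costs in safety information.** If an event is never seen among n exposed workers, the exact one-sided 95% upper bound on its risk is 1 − 0.05^(1/n). The chance of seeing at least one event of 1% incidence is 1 − 0.99^n.

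| Exposed workers analysed | Upper bound, zero events | Chance of seeing a 1% event |
|---|---|---|
| 160 (waitlist wearing excluded) | 1.85% | 80.0% |
| 200 (included, 50% control dropout) | 1.49% | 86.6% |
| 240 (included, no control loss) | 1.24% | 91.0% |

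The last two rows assume that every control still in the trial takes the device.

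**The rules side by side.** Sections {8} and {11a} exclude the period without restriction. Section {22} includes it in adverse event documentation if the trial is taken to run to the end of each 6-month wave, which section {15} suggests. No sentence says which rule governs the reporting of adverse events.

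**The case against.** The strongest reply is that the authors surely meant outcome analyses, that excluding a waitlist period is standard, and that adverse event tabulation belongs in an analysis plan or full protocol not shown here. Onset date and device relationship are recorded, so an analyst could separate the periods. The objectives list no harm objective, and the safety comparison with usual work concerns weeks 0 to 12. The gain in precision is modest.

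Much of this stands. The exclusion is right for effectiveness, and the numerical loss is moderate. It does not remove the point, because the article does more than leave a detail open. It states an unrestricted exclusion twice, and an analyst who obeys it has to leave these events out.

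Three stronger readings are tempting, and the documents do not support them.

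- **Former controls leave the harm data.** Section {22} exempts no arm and no period from documentation. What is lost is the analysis, not the collection.
- **There is no contact at all after week 12.** The two-weekly safety monitoring in section {21a} and the regular fit checks in section {22} have no stated end, and devices have to be returned to the study team. What is absent is a scheduled assessment, adverse event enquiry or training entry in Table 3.
- **Device events will be counted under the control arm.** No such tabulation is planned. The as-randomised rule in section {20a} is written for the primary analysis, and counting these events by arm would breach the exclusion in {8} and {11a}.

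**Conclusion.** The point holds as an exclusion rule that is drawn too widely and conflicts with the adverse event window. Followed as written, the safety analysis omits device exposure in up to 33% of the workers who wear the exoskeleton. On the protocol's own dropout figures the share is 27% (25% dropout) or 20% (50% dropout), and it is lower with partial uptake. These shares assume 240 randomised and all 160 intervention participants exposed. The cost is a zero-event upper bound of 1.85% instead of 1.24% to 1.49%.

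The randomised effectiveness comparison is unaffected. The plan should be changed because the correction is cheap and because the waitlist wearing is a planned half of every wave in a trial that says it will assess device safety.

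**What to change.** 1. In sections {8} and {11a}, limit the exclusion of the waitlist wearing period to effectiveness and feasibility outcomes.
2. In section {22}, define the end of adverse event collection for the individual participant. Compare adverse events by randomised arm only from enrolment to the week-12 assessment. Report adverse events and device discontinuations during waitlist wearing separately and descriptively, as non-randomised device exposure.
3. In Table 3, add a device-handover entry for controls and a short question on adverse events and stopping of device use during the waitlist period. The question would be new, but it can run on the LimeSurvey platform already in use.
4. Reconcile the enrolment-time training in section {11c} and Table 3 with the controls' later device start.

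The cost is protocol wording and a small added questionnaire burden for controls. No extra participants or staff are needed. Recruitment began in January 2026 and is expected to run to June 2027, so at the date of this protocol version (3 February 2026) nearly all waitlist wearing was still to come.
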